#### Mental Health Measures

We will administer the Patient Health Questionnaire-9 [41] to assess depressive symptoms and the 20-item Posttraumatic Stress Disorder Checklist for *DSM-5* [42] to assess posttraumatic stress disorder symptoms.

#### Quality of Life

The VR-36 [43] is a 36-item measure of health-related quality of life, including physical functioning, role limitations due to physical problems, bodily pain, general health perceptions, vitality, social functioning, role limitations due to emotional problems, and mental health. It is often summarized into physical functioning components and mental functioning components and is one of the most widely used and valid measures of physical and psychological well-being.

#### Psychological Flexibility

The MPFI [44] is a 60-item self-report measure that assesses psychological flexibility, the main mechanism of change proposed in our theoretical model. The MPFI assesses 6 dimensions of flexibility (ie, present moment awareness, self as context, acceptance, contact with values, committed action, and cognitive defusion), 6 dimensions of inflexibility (cognitive fusion, self as context, inaction, the lack of contact with values, the lack of contact with the present moment, and experiential avoidance), and 2 global composite dimensions. The MFPI is sensitive to clinical change, and its subscales have demonstrated excellent internal consistencies across several subpopulations [45].

#### Pain Acceptance

The Chronic Pain Acceptance Questionnaire (CPAQ; [46]) is a 20-item survey measuring willingness and engagement in valued life activities and domains, even during times of pain. Higher CPAQ scores indicate higher activity engagement, pain willingness, and overall pain acceptance. Pain willingness reflects a pattern of refraining from attempts to control or avoid pain, while activity engagement represents the degree of engagement in valued activities irrespective of pain. The CPAQ is a well-validated measure with high internal consistency and test-retest reliability [47].

#### Valued Living

The Chronic Pain Values Inventory [15] is a 12-item self-report measure that measures the agreement between a veteran’s values and their life. Accordance is measured across areas of living, including work, health, and family, and calculated by subtracting an “importance” rating from the “success” rating across each domain. Higher agreement with values is correlated with lower pain-related anxiety, lower overall perceived disability, and greater client functioning. These associations hold even in the context of high levels of pain [15]. Good reliability has been shown in previous studies for accordance scores across domains (Cronbach α=0.82) [32].

#### Intervention Usability

The System Usability Scale [48] is a 10-item measure rated on a 5-point Likert scale that assesses the overall usability of a system. Generally regarded cutoff scores for usability include scores of ≥68 (above average usability) and ≥80 (high usability likely to be recommended).

#### Satisfaction With Treatment

Global treatment satisfaction will be assessed using the Client Satisfaction Questionnaire-8 [49]. This 8-item scale measures the perceived quality and effectiveness of the chronic pain intervention. This scale showed acceptable internal consistency within the previous online VACT-CP pilot study (Cronbach α=0.93) [32].

#### Qualitative Semistructured Exit Interview

A semistructured 30-minute qualitative interview using open-ended questions (Multimedia Appendix 3) will be conducted after the participants complete the intervention to assess acceptability and dissemination issues. A random set of 30 VACT-CP users (n=10, 33% per site) will be identified and invited to participate until the goal of 10 interviews per site is reached. Interview questions will explore participants’ experiences with accessing and using the VACT-CP program online, perceived effects of the treatment’s core components, willingness to recommend the program to others, and any problems or concerns encountered during its use. In addition, we will inquire about past strategies or tools used to address their chronic pain issues and whether the VACT-CP treatment was more useful than previous options or strategies. Finally, participants will be asked to indicate what changes they would make to the treatment to assist in self-management of their chronic pain.

### Sample Size Considerations

The aims of this efficacy study align with the recommendations for stage 2 development of behavioral therapies [50,51]. Therefore, the primary aim of this RCT is to evaluate treatment group–related changes in pain-related functioning and quality of life outcomes. Secondary aims include examining whether the expected mechanism of behavior change (psychological flexibility) mediates the relationship between pain severity and pain-related functioning for veterans receiving VACT-CP. We expect VACT-CP will produce a small to medium treatment effect consistent with previous ACT studies [28].

We will use mixed effects modeling to test for a time by intervention interaction. Our power analysis and sample size estimation is based on our primary outcome, and research suggesting a clinically meaningful desired difference of 1 point on the BPI-Interference [52]. We expect the correlation between time points to be approximately 0.2 based on current preliminary data. To achieve a desired power of 0.80 and a type I error rate of 0.05 to detect a difference of 1 between the (fixed) group means, we estimate that we will need a minimum of 128 participants, with 64 participants per group. To ensure sufficient power for the planned aim 3 mediation analyses (focused on investigating ACT processes within the VACT-CP group), we will over-recruit in the VACT-CP arm to meet the recommended minimum sample size of 120 participants for mediation analysis. We will use path analysis to model the main independent variable X (pain severity), the mediator M (change from baseline to end of treatment in psychological flexibility as measured using the MPFI), and the main outcome variable Y (pain-related functioning) after treatment and at 3-month and 6-month follow-ups. We have thus used a more conservative group size estimate of 80 in the active control group and 120 in the VACT-CP group to fully power both the efficacy evaluation (hypotheses 1 and 2) and the mediational analyses (hypothesis 3).

With an expected attrition rate of 20% based on pilot data, we will obtain consent from up to 240 participants to allow for successful randomization of a total sample of 200 participants. It is possible that attrition will be greater for some clinical groups than for others (eg, veterans with additional symptoms related to a comorbid mental health issue). Therefore, variables of interest may be associated with attrition, and missing data will not be at random, which could then introduce bias in results despite randomization. To address this possibility, we will attempt to determine whether missing data are missing at random or missing completely at random. We will do so by investigating whether baseline measures (depression symptom severity and posttraumatic stress disorder symptom severity) predict attrition and whether statistical testing suggests that data are not missing at random, and we will modify analyses accordingly (eg, via stratification).

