### Participant Recruitment

Veterans (N=200) will be recruited and enrolled over the course of 30 months (with a target monthly enrollment rate of 2-3 veterans per site) from 3 US VA medical centers (Bedford, Massachusetts; Dallas, Texas; and West Haven, Connecticut). Recruitment will be conducted through methods such as the distribution of study flyers and information at outreach events and clinics within the VA, mailers sent to veterans identified through medical record reviews, and social media advertisements. We will randomize 200 veterans in a 2:1 ratio, with 120 (60%) veterans assigned to VACT-CP (treatment condition) and 80 (40%) veterans assigned to Online Pain School. Eligibility will be determined based on inclusion and exclusion criteria following a phone screening, medical record review, and abbreviated diagnostic interview during the baseline appointment. The inclusion criteria are (1) current diagnosis of noncancer chronic pain, defined by at least one pain-related diagnosis indicated by an *International Classification of Diseases, 9th Revision* or *International Classification of Diseases, Tenth Revision* code related to either musculoskeletal pain or joint problems or Osteoarthritis and minimum of a grade 1 (mild) or 2 (bothersome) on the Graded Chronic Pain Scale–Revised; (2) possession of a computer and working, high-speed wireless internet connection at home; (3) competency to provide written informed consent; and (4) aged ≥18 years. Individuals with chronic pain who do not meet the inclusion criteria will be provided with resources for VA-delivered pain management care. Exclusion criteria will include (1) any current or lifetime *Diagnostic and Statistical Manual of Mental Disorders, 5th Edition (DSM-5)* psychotic disorder; (2) current or recent diagnosis or treatment of (within 1 month of study entry) *DSM-5* substance use disorder; (3) current use of any other chronic pain–related psychological treatment; (4) clinically significant suicidality within the past year as defined by past-year suicidal behaviors or suicide attempts; and (5) any cognitive or physical impairment that would interfere with study participation or using a computer and providing feedback. Exclusion criteria (1), (2), and (4) will be assessed through baseline interviews (ie, *the Structured Clinical Interview for DSM-5* [34]) and medical record reviews. Participants with additional, comorbid pain diagnoses will not be excluded.

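### The 240-consent ceiling does not match 20% attrition, and no allowance for loss after randomisation is added to the 120 VACT-CP participants named as the minimum for the mediation analysis

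*Protocol article*

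**What the plan says.** All of the sizing is in the protocol article under Sample Size Considerations. For efficacy, "we estimate that we will need a minimum of 128 participants, with 64 participants per group". For the mediation analysis within the VACT-CP arm, "we will over-recruit in the VACT-CP arm to meet the recommended minimum sample size of 120 participants for mediation analysis". The chosen sizes of 80 and 120 are said "to fully power both the efficacy evaluation (hypotheses 1 and 2) and the mediational analyses (hypothesis 3". Participant Recruitment gives the same split: "with 120 (60%) veterans assigned to VACT-CP (treatment condition) and 80 (40%) veterans assigned to Online Pain School".

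The attrition allowance follows: "With an expected attrition rate of 20% based on pilot data, we will obtain consent from up to 240 participants", and the purpose is given as "to allow for successful randomization of a total sample of 200 participants". The rest of that paragraph treats attrition as something that may differ between clinical subgroups, produce missing data and bias the results even though the trial is randomised. It plans to check whether baseline depression and PTSD scores predict it.

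Primary Analyses defines the mediation model. Its mediator is the change in psychological flexibility (MPFI) from baseline to end of treatment. Its outcome is BPI-Interference at 3 months, with repeat analyses after treatment and at 6 months.

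**The concern.** There are two separate problems in one paragraph.

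First, the consent figure looks like the familiar slip of multiplying the target by one plus the loss rate instead of dividing by one minus it. Since 240 is worded as an upper limit, sites could not simply consent more to make up the difference.

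Second, one rate appears to serve two different losses. As written, the 20% is used up between consent and randomisation. The sentences after it describe participants who are randomised and then fail to supply outcomes. Nothing is added for that second loss, although the VACT-CP arm is set at exactly the mediation minimum and so has no margin.

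The secondary mechanism aim is what is at stake. Study Trial Design and Study Procedures both give the within-arm mediation analysis as the reason for unequal allocation. If the analysable VACT-CP number falls below 120, the plan no longer meets the criterion on which it chose that allocation.

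**Working it through.** **Inputs, all from the protocol article.** Attrition 20%; consent ceiling 240; randomised 200 (120 VACT-CP, 80 Online Pain School); mediation minimum 120 in VACT-CP; efficacy minimum 64 per group, with power 0.80 and two-sided α 0.05.

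**1. The consent figure.**
- The plan's number is reproduced by 200 × (1 + 0.20) = 240.
- The number that leaves 200 after a 20% loss is 200/(1 − 0.20) = 250.
- Forward check: 240 × 0.80 = 192, which is 8 short of 200.
- Loss that 240 can absorb: 1 − 200/240 = 16.7%.

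**2. Loss after randomisation, if that is what the 20% describes.**
- VACT-CP: 120 × 0.80 = 96, which is 120 − 96 = 24 below the stated minimum.
- Online Pain School: 80 × 0.80 = 64.
- Total: 96 + 64 = 160.
- Other rates for the VACT-CP arm (assumed): 10% leaves 108; 16.7% leaves 100; 25% leaves 90. Because the arm starts at the minimum, any loss takes it below.
- For scale, keeping 120 complete cases at 20% loss would take 120/0.80 = 150 randomised to VACT-CP.

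Steps 1 and 2 are alternative readings of the same 20%. The 96 comes from 120 × 0.80 and does not depend on the 192.

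**3. Does the efficacy comparison suffer?** The equal-group equivalent of n₁ versus n₂ is 2n₁n₂/(n₁ + n₂).
- 96 versus 64: 2 × 96 × 64/160 = 76.8 per group.
- The article also calls the allocation 2:1, which 120:80 is not. A true 2:1 split of 200 is about 133:67. After 20% loss that is about 107 versus 53, giving 2 × 107 × 53/160 = 70.9 per group.
- Both exceed 64. The article states no SD. Assuming a standardised difference of 0.5, which reproduces 64 per group at power 0.80, two-sample t-test power is about 0.87 for 96 versus 64 and 0.84 for 107 versus 53.

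Under that true 2:1 split the VACT-CP arm would keep about 107, still below 120.

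**The case against.** The strongest reply is that the text ties the 20% only to getting from consent to randomisation. On that reading the article gives no rate for later loss, and 96 cannot be derived from it. This is fair, and it is why the two readings must be kept apart. It does not rescue the plan: on that reading 240 is the wrong ceiling, and the later loss that the paragraph goes on to discuss still has no allowance. Two features favour the other reading: the missing-data discussion itself, and the fact that 80 × 0.80 equals the 64 controls required.

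A second reply is that 96 counts complete cases. A structural equation model fitted by full-information likelihood would keep partly observed participants, those who stop the intervention are still followed, and loss by end of treatment may be less than 20%. This stands in part. The article commits to using all available data for the mixed models but says nothing similar for the mediation model. Participants lost early would still lack the mediator change, the outcome or both.

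Third, 120 is a recommended minimum with no derivation shown, and whether it means enrolled or complete participants is not stated. That also stands. The shortfall is against the plan's own headcount, not against a power calculation.

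Three stronger conclusions might be inferred, and the documents support none of them:
- **That the 240 error causes the 96.** It does not; they belong to different readings.
- **That hypothesis 1 is underpowered, because controls fall to 64 or even 53.** The larger VACT-CP arm more than compensates.
- **That mediation power drops by a definite amount.** The article gives no path sizes, and the answer depends on them. In simulations of the bias-corrected bootstrap with an assumed direct path of 0.3, standardised paths of 0.26 and 0.26 give power of about 0.65 at 96 and 0.77 at 120; 0.30 and 0.30 give about 0.8 and 0.9; 0.35 and 0.35 give about 0.95 and 0.98. With the smallest of these paths 120 is itself short of 0.80. With the largest, 96 is ample.

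**Conclusion.** The point holds in two separate parts. The consent ceiling is wrong for the stated rate: 240 where 20% loss requires 250, a shortfall of 8 randomised participants (4% of 200) if the 20% falls before randomisation. That part is small and threatens no efficacy claim.

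The second part matters more. The mediation arm has no margin for loss after randomisation, although the paragraph itself expects such loss. If the 20% applies there, and if partly observed participants are not used, about 96 remain against a stated minimum of 120. The statement that hypothesis 3 is fully powered is then unsupported by the plan's own numbers. What is established is a shortfall of 24 in headcount for a secondary aim. The resulting loss of power cannot be fixed from the document. The efficacy comparison keeps the equivalent of about 71 to 77 per group against 64 required.

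**What to change.** State which loss the 20% describes, and treat the two losses separately.

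- **If it is loss between consent and randomisation:** change the ceiling from 240 to 250, and give the expected loss after randomisation as its own figure, with the analysable VACT-CP number that follows from it.
- **If it is loss after randomisation:** restate the expected analysable sample as about 160 (96 VACT-CP, 64 Online Pain School) and withdraw the full-power statement for hypothesis 3. Then either give the power or detectable indirect effect at about 96, with the assumed paths stated, or specify full-information likelihood for the structural equation model so that partly observed participants are kept.

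The cost is wording, up to 10 more consents, and a less favourable stated figure for a secondary aim. No more participants need to be randomised.

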To investigate the proposed mechanism of change in VACT-CP (hypothesis 3), we will analyze whether BPI-Interference subscale improvements are mediated by psychological flexibility after treatment and at 3-month and 6-month follow-ups. Similar to previous ACT process mediation procedures [53], structural equation modeling and a bias-corrected bootstrap approach will be used to examine the indirect effect of pain severity on pain-related functioning through pretreatment and posttreatment changes in psychological flexibility. We will model the main independent variable X (pain severity as measured by the BPI-Severity subscale), the mediator M (change from baseline to end of treatment in psychological flexibility as measured by the MPFI), and the main outcome variable Y (pain-related functioning as measured by the BPI-Interference subscale) at 3 months after intervention. A bias-corrected bootstrap procedure with 3000 bootstrap samples will be used to produce a 95% CI around the mediation effect estimate. A 95% CI excluding zero will be interpreted to be statistically significant at a *P*<.05 level. In accordance with previous mediation methods [54], mediation will be assumed demonstrated if paths X and Y and XY (the indirect effect) are statistically significant based on acceptable or adequate model fit. Model fit will be assessed using the chi-square goodness-of-fit statistic and approximate fit indices, including root mean square error of approximation, the goodness-of-fit index, the standardized root mean square residual, and the chi-square/*df*. We will repeat this analysis for posttreatment and 6-month time points as well. This analysis can provide further support for the mechanisms by which the ACT intervention works as well as evaluate the potential longevity of ACT process changes on pain-related functioning.

Additional data will be provided by the Client Satisfaction Questionnaire-8 and semistructured qualitative interviews with VACT-CP users (n=30) as well as by tracking website use information and calls or emails to research staff with concerns. Analysis of the postintervention interviews will be done using notes taken by one of the team members during the exit interview; interviews will also be audio recorded and transcribed. Study staff will apply qualitative analytic techniques to these data (eg, coding for and extracting major themes) to assess both barriers to and facilitators of the use of the VACT-CP system. A modified consensual qualitative research (CQR) approach [55] will be used to code the transcribed videos. CQR can be particularly useful in allowing a team of coders to identify themes arising in both structured and more open-ended interview moments. An initial codebook will be developed using coding based on the key activities and questions in the user testing protocol. These procedures are based, in part, on the successfully piloted interview procedures and script from the initial VACT-CP pilot study. Primary research staff will use the previous pilot codebook in identifying use, usability, and usefulness themes within the interviews. The initial codebook will be used by 2 to 3 coders throughout the data analysis process to foster multiple perspectives until consensus is reached among the coders about the meaning of the data. In addition, at least 1 auditor will check the work of the primary team of coders and serve to minimize potential bias. We will report the frequency of emerging domains and themes. Themes will then be categorized according to the following CQR groupings: general (includes all or all but 1 of the cases), typical (includes half or more of the cases up to the cutoff for general), and variant (at least 2 cases up to the cutoff for typical). We will use these data to discuss broader scientific and implementation-related barriers and facilitators for interventions for patients with chronic pain within the VA system. The themes generated by these data will be used to identify usability issues, perceived usefulness of VACT-CP, and potential areas for revision. The qualitative usability and usefulness information will be triangulated with quantitative data and incorporated into the primary outcome manuscript on VACT-CP efficacy.

## Results

Participant recruitment began in January 2025 and is expected to be completed by January 2027. Data collection is expected to be completed by June 2027, and primary data analyses are expected to be completed by early 2028.

## Discussion

### Potential Applications

A substantial gap remains in the availability of at-home pain self-management treatment options to help veterans increase their functioning and quality of life in the context of their chronic physical, psychological, and social concerns. The VACT-CP program, available at any time and to any veteran with internet and computing technology access, is innovative in its approach and has several potential applications. First, VACT-CP is the only VA-developed and tested website program for chronic pain support and has the potential to improve access to chronic pain treatment for veterans. Further, unlike many online self-management apps and online programs within VA, the VACT-CP treatment uses ACT as an evidence-based alternative to traditionally available and in-person chronic pain treatments (eg, Cognitive Behavioral Therapy for Chronic Pain) to extend treatment targets to pain acceptance and value-based living. Thus, VACT-CP has the potential to add needed emphasis to at-home treatment targets, such as pain-related functional improvement and quality of life. In addition, VACT-CP is uniquely interactive, as the 7-module program is guided by the novel use of an ECA, “Coach Anne,” who can provide user-centered feedback and tailoring through interactive dialogue, assessments, and exercises. The focus on interactive, personalized care has the potential to enhance treatment engagement for veterans. Finally, consistent with VA priorities and clinical guidelines, VACT-CP could improve access to a nonpharmacological pain management treatment option that is readily available to veterans experiencing chronic pain to allow them to gain and sustain a self-care and treatment skill set that applies to both chronic pain and common co-occurring conditions (eg, depression, anxiety, and substance misuse).

